### Study population and site

The University of Illinois Medical Center (UIMC) includes both inpatient and outpatient facilities serving a diverse, low-income population in Chicago. There are approximately 8,000 unique African American or Latino individuals receiving care for diabetes in the outpatient setting annually. The UIMC has multiple off-site ambulatory centers staffed by Family Practice and Internal Medicine primary care physicians (PCPs), and include affiliated Federally Qualified Health Centers (FQHCs). We anticipate participation of 6–8 clinical entities in the study. All sites share access to the electronic medical record (EMR), Cerner Powerchart (Cerner Corporation, Kansas City, MO).

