### Identification, recruitment, and randomization of participants

The recruitment process will be carried out separately for each ambulatory site as determined by the project coordinator and clinical staff. On-site research assistants (RAs) will receive referrals from staff or patients interested in being screened for the study. All participant medical records are reviewed by a study physician to ensure A1c eligibility. Individuals deemed eligible will be scheduled for an appointment at the university Clinical Interface Core facility to complete written consent, HIPAA authorization, and baseline data collection. The RAs will inform patients that the research is being conducted to improve medication management in diabetes care and to find out whether pharmacists and health promoters help people reach goals of therapy. The RAs will spend additional time discussing the study protocol in detail as part of consent procedures and use the “teach-back” method to ensure participant comprehension [30].

Randomization to receive either *Pharmacist* or *Pharmacist+HP* assignments for the first year will occur after consent and completion of all baseline data collection. A random sequence of 300 participant assignments will be used. Blocked randomization will ensure that allocation to experimental conditions will be balanced within four gender by ethnicity subgroups at each site. The project coordinator will independently determine group assignments and will log the information separately. Baseline results for A1c and fasting lipid profile are entered into the patient’s medical record by a study physician and electronically shared with the primary care physician and pharmacist.

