### Sample size calculation

Sample size calculations are powered to detect change in A1c. Based on a previous study [31], we estimated a mean baseline A1c level of 10.0% with standard deviation of 1.8% and an effect size of (1.0/1.8) 0.56. The cross-time correlation was estimated to be 0.30. We adjusted for clustering, assuming an intraclass correlation coefficient (ICC) of 0.02 and cluster size of 30, which yields a design effect of 1.58. Two-sided alpha of 0.05 and 80% power are assumed requiring a minimum of 114 per group. Allowing for an estimated 10% drop-out during each of the two years, approximately 150 patients will be required for each group (or 300 total).

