### Data analyses

Data will be analyzed for clinical effectiveness using intention-to-treat principles [32-34]. To represent dropouts in the analysis, missing data will be imputed using various approaches, such as “last value carried forward.” The Little and Yau “return to baseline” imputation rule, in which any gains over baseline levels dissipate upon dropout, will be used for primary analyses. Patients who share a single primary care physician (PCP) or health promoter (HP), might exhibit similarities that are not shared with patients attended to by other physicians. To address this, we will include random effects in the model for clinic site, PCP, and HP. We will include as predictors relevant care and treatment-related variability such as medication therapy intensifications and clinical encounter frequency.

We will test the hypothesis that A1c, blood pressure, and LDL-cholesterol levels will be lower and diabetes behaviors (including medication adherence) will be improved with patients receiving *Pharmacist+HP* compared with those receiving *Pharmacist* alone. Univariate comparisons between the two study groups with respect to outcome measures and covariates at baseline will be conducted using Chi-square tests for categorical variables, Kruskal-Wallis tests for ordinal variables, and linear mixed models for continuous variables. Non-normal continuous data will be transformed prior to linear model analyses. The baseline variables include demographic, therapy complexity, and health literacy data. If we find any between-group differences at baseline, we will adjust for this in our primary multivariate analyses by including relevant covariates.

We will also extend the usual analysis of crossover designs by including a longitudinal trend component in the first year. Thus, we can examine the time course (0, 6, and 12 months) as linear or quadratic over the first three measurements. This will allow us to investigate whether changes are made early, and at what rate they continue through the rest of the time period. This analysis permits the comparison of trends between *Pharmacist* and *Pharmacist+HP* conditions. In addition, we will regard participants as a random effect and will use Gaussian mixed-model estimations (SPSS MIXED command). We can then substitute treatment by period interactions for the carry-over effects, and the model can be reduced in a recommended sequence (first omit carry-over, then omit treatment, finally omit period).

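### Covariates for the primary model are chosen by testing baseline differences between randomised groups, so the model depends on chance imbalance and not on prognostic value

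*Protocol article*

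**What the plan says.** In the protocol article, Data analyses, the two arms are first compared on their baseline outcomes and covariates, one variable at a time. These comparisons, the text says, "will be conducted using Chi-square tests for categorical variables, Kruskal-Wallis tests for ordinal variables, and linear mixed models for continuous variables". The candidates are described by class: "The baseline variables include demographic, therapy complexity, and health literacy data". The consequence for the primary analysis follows directly: "If we find any between-group differences at baseline, we will adjust for this in our primary multivariate analyses by including relevant covariates".

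The section on identification, recruitment and randomization places allocation after consent and all baseline data collection, and restricts it: "Blocked randomization will ensure that allocation to experimental conditions will be balanced within four gender by ethnicity subgroups at each site".

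The terms that Data analyses names unconditionally are the clustering terms ("we will include random effects in the model for clinic site, PCP, and HP"), participant as a random effect, and care variables ("We will include as predictors relevant care and treatment-related variability such as medication therapy intensifications and clinical encounter frequency"). Gender and ethnicity are not named. They could enter as demographic variables that happen to differ, or as factors in the exploratory subgroup analyses.

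**The concern.** A baseline test between randomised arms asks whether an observed difference could be chance. With sound randomisation the answer is already known: it is. The result therefore does not show which variables need adjustment. A strong predictor of A1c that happens to balance stays out, and a weak one that happens to differ comes in. No threshold is given for the tests, and which covariates count as relevant is not defined. The form of the primary model is thus settled only after the arms have been compared.

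The rule also works against the randomisation strata. Blocking keeps gender and ethnicity balanced, so a test for imbalance will hardly ever select them. At stake are a primary estimate fixed in advance, precision from prognostic baseline variables, and agreement between the analysis and the restricted randomisation.

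**Working it through.** **1. The plan's own figure, to identify the quantity it is powered on.** The Sample size calculation section gives "standard deviation of 1.8% and an effect size of (1.0/1.8) 0.56", cross-time correlation 0.30, design effect 1.58, two-sided alpha 0.05, 80% power and 114 per group.
- SD of change = 1.8 × √(2 × (1 − 0.30)) = 2.13.
- n = 2 × (1.96 + 0.842)² × 2.13² / 1.0² = 71.2, rounded up to 72.
- 72 × 1.58 = 113.8, so 114. The figure reproduces.
- Using the follow-up value alone, n = 50.9, rounded up to 51, and 51 × 1.58 = 80.6, so 81. That does not match.

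The trial is therefore powered on change in A1c, as the section says. This matters in step 4.

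**2. How often the rule would be triggered.** For k independent tests at 5%, the chance of at least one flag is 1 − 0.95^k. The protocol fixes neither k nor the 5%, so both are assumptions, as is independence.

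| k | chance of at least one flag |
|---|---|
| 5 | 23% |
| 10 | 40% |
| 15 | 54% |
| 20 | 64% |

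The upper end is plausible. The Study measures section lists about a dozen socio-demographic items, four diabetes-history items and health literacy, and Data analyses adds therapy complexity and the baseline outcomes.

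**3. Whether the rule could select gender or ethnicity.** On the number of sites the protocol says: "We anticipate participation of 6–8 clinical entities in the study". Assume 7 sites, so 7 × 4 = 28 cells, with N = 300, blocks of 4, and gender and ethnicity each split 50:50.
- An arm imbalance within a cell arises only from its last incomplete block. With 0, 1, 2 or 3 patients left over, the variance of the difference is 0, 1, 4/3 or 1. The average is 0.83.
- For the gender comparison the total variance is 28 × 0.83 = 23.3, against 300 under simple randomisation.
- The test statistic then has SD √(23.3/300) = 0.28 instead of 1, so the 1.96 threshold lies 1.96/0.28 = 7 SDs out.

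A simulation under the same assumptions (three scenarios, 4,000 runs each) flagged gender or ethnicity in 0% of runs.

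**4. What omitting the strata costs.** Let R² be the share of variance in the analysed quantity that the strata explain. With arms balanced within strata, an analysis that omits them overstates the SE by 1/√(1 − R²), and the true type I error is 2 × (1 − Φ(1.96/√(1 − R²))). No document gives R², so 2%, 5% and 10% are assumed.

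| R² | SE overstated by | type I error, follow-up level |
|---|---|---|
| 2% | 1.0% | 4.8% |
| 5% | 2.6% | 4.4% |
| 10% | 5.4% | 3.9% |

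For change from baseline, a stratum effect that is the same at every visit subtracts out. R² for the change is then 0, and type I error is 5%.

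Two simplified simulations of the level and change comparisons agree in direction. For R² of 2%, 5% and 10%, type I error for follow-up level was 0.043 and 0.048, 0.042 and 0.040, and 0.037 and 0.039. For change it was 0.047 and 0.048, 0.049 and 0.047, and 0.048 and 0.050.

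**The case against.** The strongest reply concerns the strata. The protocol powers on change, models months 0, 6 and 12 with participant as a random effect, and compares trends between arms. In that contrast a time-constant effect of gender or ethnicity cancels, so leaving it out costs essentially nothing. This stands. A reader might infer that the trial's type I error is 3.9%, or that its standard error is necessarily too large. The documents do not support either. Those figures need a comparison of follow-up levels and an assumed prognostic strength. Strata effects on the change itself would matter, but their size is unknown.

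A second reply is that a condensed article need not list every model term, and the analysis plan is not shown. This also stands as far as it goes: that gender and ethnicity go unnamed does not prove they will be omitted. It does not cover the conditional rule, which the protocol states outright for the primary analysis. An analysis plan would have to inherit the rule or contradict it.

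Third, the reference to relevant covariates leaves room for judgement, so a flagged variable need not enter the model. That is fair, and the 23% to 64% is the chance of a flag, not of a changed model. But undefined judgement exercised after the arms have been compared does not make the model pre-specified.

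Fourth, baseline A1c is already used as the month-0 measurement in the longitudinal model. That is correct, so loss of precision from ignoring baseline A1c should not be claimed.

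**Conclusion.** The point holds for the test-then-adjust rule. It makes the primary model depend on chance imbalance and does not choose covariates for prognostic value. This conclusion rests on the protocol's wording and on randomisation alone. The 23% to 64% chance of a flag is an illustration that assumes 5 to 20 independent tests at 5%.

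The strata are a secondary matter. The rule would almost never bring in gender or ethnicity, and the text does not otherwise name them. The consequence is small: no bias, and at most a mildly conservative test. Type I error is about 4.8% to 3.9% for follow-up levels if they explain 2% to 10% of A1c variance, and about 5% for change when their effect is constant over time. Site, the third factor in the randomisation, is already in the model as a random effect.

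The wording should be corrected before the arms are compared, but the defect does not invalidate the trial.

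**What to change.** In Data analyses:
- Delete the sentence that makes covariate adjustment conditional on baseline differences.
- Name the primary model terms in advance: treatment, visit, treatment by visit, gender, ethnicity and site. Site may stay a random effect.
- State whether the baseline value of the outcome enters as a covariate or as the month-0 response. It should not be both.
- Move any adjustment for chance imbalance to a sensitivity analysis, beside the secondary MANOVA analyses of inhomogeneous baseline variables that the same section already plans.

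The cost is analysis wording only. Gender, ethnicity, site and the baseline outcomes are already collected, and the sample size of 300 does not change.

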The primary analysis of each outcome in the repeated measures design will be conducted in a general linear mixed model framework. In addition, SPSS MANOVA (for repeated measures) will be used to explore the simultaneous impact of the treatment on multiple correlated dependent variables, including the use of Roy-Bargmann stepdown F-tests and discriminant function analysis as post hoc tests to identify subsets of outcome measures affected [35]. SPSS MIXED will be used to explore patterned covariance structures such as compound symmetry and autoregression along with incorporating time-varying covariates, such as depression. MANOVA secondary analyses will explore the impact on results of inhomogeneous baseline variables. Exploratory subgroup analyses will determine which participants in the intervention group had the greatest improvement in outcomes, based on demographic factors, health literacy, and medication regimen. Group by time-trend interaction contrasts also will be used to explore different group trajectories of change. In addition, we will investigate the potential consequences of medication intensification (e.g., initiation of insulin) by evaluating changes in body mass index and severe hypoglycemia.

We will explore diabetes-related behaviors (including eating habits, physical activity, and medication adherence) as well as medication treatment intensification as alternative mediators using MPlus [36]. We will also test the hypothesis that diabetes behaviors and clinical outcomes will be maintained one year after phase-out of HP support. Finally, we will test the hypothesis that diabetes behaviors and clinical outcomes improved by adding HP support after one year of *Pharmacist* alone.

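### From the second outcome on, the exploratory stepdown F-tests do not test whether an outcome is affected, so they can flag an unaffected outcome or miss an affected one

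*Protocol article*

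**What the plan says.** The Data analyses section of the protocol article sets out the confirmatory aim first: "We will test the hypothesis that A1c, blood pressure, and LDL-cholesterol levels will be lower and diabetes behaviors (including medication adherence) will be improved" under pharmacist plus health promoter care. It then fixes the main method: "The primary analysis of each outcome in the repeated measures design will be conducted in a general linear mixed model framework".

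A further layer follows. "SPSS MANOVA (for repeated measures) will be used to explore the simultaneous impact of the treatment on multiple correlated dependent variables", and the tools for that step are listed as "including the use of Roy-Bargmann stepdown F-tests and discriminant function analysis as post hoc tests to identify subsets of outcome measures affected". So the article states both the tool and the question the tool is to answer: which outcomes did the intervention affect?

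Two other statements bear on the point. The outcomes are described as correlated. Diabetes behaviours are also to be explored, "as well as medication treatment intensification as alternative mediators using MPlus", which places them on the path from treatment to the clinical outcomes.

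**The concern.** To say that an outcome is affected is to say that its mean differs between arms. A Roy-Bargmann stepdown F asks this only for the first outcome entered. Each later outcome is tested with the earlier ones as covariates, so its null hypothesis is that no arm difference remains once those earlier outcomes are held fixed. The covariates are themselves results of treatment.

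The two null hypotheses agree only if the earlier outcomes are unaffected or are uncorrelated with the later one. The plan expects neither. If a behaviour were entered before A1c, for example, the stepdown F for A1c would remove whatever part of the effect runs through that behaviour, and that is part of what the trial hopes to show.

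At stake is the list of affected outcomes drawn from the MANOVA. It could include an outcome that treatment does not change or leave out one that it does. It could also disagree with the per-outcome mixed models without any warning that the two answer different questions.

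**Working it through.** **Inputs from the article (Sample size calculation).** "standard deviation of 1.8% and an effect size of (1.0/1.8) 0.56"; "The cross-time correlation was estimated to be 0.30"; ICC 0.02 with clusters of 30; two-sided alpha 0.05; power 80%; 114 per group. The 0.30 relates one outcome to itself over time. It is not a correlation between outcomes, and no such correlation is given.

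**The plan's own figure.**
- Design effect: 1 + (30 − 1) × 0.02 = 1.58.
- Change-score formula: 2 × [1.8 × (1.960 + 0.842)/1.0]² = 50.9; × 2(1 − 0.30) = 71.2; × 1.58 = 112.5. Rounding 71.2 up to 72 before inflating gives 72 × 1.58 = 113.8, so 114. The figure reproduces, with power 0.805.
- Effective size per arm: 114/1.58 = 72.

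**What the second step tests.** Let both outcomes have within-arm SD 1, effects d1 and d2, and correlation rho. The adjusted arm difference is d2 − rho·d1, and its residual SD is √(1 − rho²).
- If d2 = 0, the tested effect is −rho·d1. At d1 = 0.56 and rho = 0.3 it is −0.17. With benefit scored as positive, an outcome with no effect looks harmed.
- If d2 = rho·d1, the tested effect is zero although the outcome is affected.

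**Hand check at rho 0.3, n = 72 per arm.** The standard error is about √(1 − 0.09) × √(2/72 + 0.56²/142) = 0.954 × 0.173 = 0.165.
- Unaffected outcome: 0.168/0.165 = 1.02 standard errors. Against a critical value of 1.98 this gives rejection of about 0.17.
- Full effect: (0.56 − 0.168)/0.165 = 2.37, which gives power of about 0.65.

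**Simulation** (two normal outcomes at one time point, first outcome affected by 0.56 SD, n = 72 per arm, nominal 0.05, 6,000 trials per setting):

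| rho | d2 = 0: stepdown | d2 = rho·0.56: stepdown / unadjusted | d2 = 0.56: stepdown / unadjusted |
|---|---|---|---|
| 0.2 | 0.10 | 0.05 / 0.10 | 0.75 / 0.92 |
| 0.3 | 0.17 | 0.05 / 0.17 | 0.65 / 0.92 |
| 0.4 | 0.28 | 0.05 / 0.27 | 0.55 / 0.92 |
| 0.5 | 0.45 to 0.47 across runs | 0.05 / 0.39 | 0.45 / 0.91 |

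The unadjusted test of an unaffected outcome stays near 0.05 throughout. The stepdown rate is 0.05 at rho 0 and about 0.06 at rho 0.1. Requiring a significant overall MANOVA first changes the rates by at most about 0.3 percentage points.

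**Sensitivity, unaffected second outcome, rho 0.2, 0.3 and 0.5.**
- First effect 0.47 SD (change-score SD 1.8 × √1.4 = 2.13, and 1.0/2.13 = 0.47): 0.09, 0.14, 0.35.
- First effect 0.28 SD (half of 0.56): 0.06, 0.08, 0.16.
- 150 per arm with no allowance for clustering, first effect 0.56 SD: 0.16, 0.32, 0.77.

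**Discriminant analysis, d = (0.56, 0), rho 0.5.** The weights are proportional to the inverse correlation matrix times d. The second weight is −0.5 × 0.56/(1 − 0.25) = −0.37, which is not zero although the outcome is unaffected. Its structure coefficient is proportional to d2 and so is exactly 0.

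**The case against.** The strongest reply is that the right analysis is already the primary one. Each outcome has its own mixed model, the MANOVA is described only as a way to explore, and the stepdown tests are post hoc to it. That stands, and it limits the reach of the point. A reader might infer that the trial's main conclusions or its sample size are compromised. The article does not support that, because neither depends on the stepdown tests.

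A reader might also infer that every stepdown test is wrong and that misclassification is certain. It is not: the first outcome in the order is tested unadjusted, and the error rates vanish at rho 0 and are small at rho 0.1 or when the first outcome is only weakly affected. Rates computed on independent patients, such as 0.77 at 150 per arm and rho 0.5, overstate the problem because they ignore the plan's own design effect.

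Two further inferences should be resisted. The absence of a stated order of entry is no defect here, since a fuller protocol or analysis plan may give it. Nor is discriminant analysis unsuitable as a whole: the article does not say whether weights or structure coefficients will be read, and only the weights are conditional.

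The mismatch itself survives these replies. The article states what the stepdown tests are for, no order of entry turns the later steps into unadjusted tests, and exploratory status does not make a test answer a different question.

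**Conclusion.** The point holds for the exploratory MANOVA step only. From the second outcome on, the stepdown F-tests answer whether an outcome adds to the arm separation already shown by earlier outcomes, not whether it is affected.

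The direction of the problem follows from the algebra. Its size rests on assumptions: the between-outcome correlation, a strongly affected outcome placed first, two outcomes at a single time point, and clustering handled through an effective 72 per arm. Under these, at correlations of 0.2 to 0.5, false flags run from twice to about nine times the nominal 5%, and power for an outcome with the full 0.56 SD effect drops to between 0.75 and 0.45. With a first effect of 0.47 SD, the false flags run from 0.09 to 0.35.

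This should be corrected because the rule as stated can give a wrong answer to its own question and the correction is nearly free.

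**What to change.** Amend the sentence on post hoc tests in the Data analyses section as follows.

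1. Identify the affected outcomes from the unconditional arm contrasts in the general linear mixed models already planned, meaning contrasts that do not adjust for the other outcomes.
2. Keep the stepdown F-tests, if wanted, only to describe whether an outcome adds information beyond those entered before it. State that they are not evidence that an outcome is or is not affected.
3. If discriminant analysis is used to name affected outcomes, read the structure coefficients and not the weights.

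A multiplicity adjustment across outcomes, such as Holm, is optional and costs a little power per outcome. The change needs a sentence or two of text. It needs no new data, no further patients and no new models.

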### Study design

The proposed study is a randomized trial with crossover after one year (Figure 1). Three hundred African-American and Latino patients with uncontrolled type 2 diabetes will be randomized to receive either:

1. *Pharmacist*: Clinical pharmacists will provide medication and disease management services to patients following a Pharmacist Management Protocol.

2. *Pharmacist+HP*: Includes clinical pharmacist services, plus a health promoter who will attend to both lifestyle and medication adherence-related issues by identifying barriers, solving problems, and providing support through home visits and telephone contact.

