### Inclusion criteria

Patients will be eligible for the study if they: (a) are self-identified as Latino/Hispanic or African-American; (b) have verbal fluency in English or Spanish; (c) are age 21 or above; (d) have a history of type 2 diabetes; (e) have an elevated A1c level 8% or higher in the past year (confirmed through EMR); (f) received primary care at UIMC for at least one year; and (g) take at least one oral medication for diabetes or hypertension (for adherence assessment).

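### The exploratory subgroup analysis ranks improvement inside the Pharmacist+HP arm only, so it cannot separate health promoter benefit from pharmacist response, time and possible regression to the mean

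*Protocol article*

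**What the plan says.** All references are to the protocol article.

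- **Data analyses**, on subgroups: "Exploratory subgroup analyses will determine which participants in the intervention group had the greatest improvement in outcomes, based on demographic factors". The other two factors named there are medication regimen and health literacy. The quantity is improvement, the population is one arm, and the label is exploratory.
- **Data analyses**, next sentence: "Group by time-trend interaction contrasts also will be used to explore different group trajectories of change". This compares the two arms' trajectories and contains no subgroup factor. The between-arm hypotheses in the same section contain none either.
- **Study design**, on the Pharmacist+HP arm: "Includes clinical pharmacist services, plus a health promoter who will attend to both lifestyle and medication adherence-related issues". The comparator receives the same pharmacist services without the HP.
- **Inclusion criteria**: patients must "have an elevated A1c level 8% or higher in the past year", confirmed from the medical record.
- **Sample size calculation**, on the A1c assumptions: "we estimated a mean baseline A1c level of 10.0% with standard deviation of 1.8% and an effect size of (1.0/1.8) 0.56". On how closely repeated A1c values are related, the same paragraph adds: "The cross-time correlation was estimated to be 0.30".

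**The concern.** The trial asks what an HP adds to a pharmacist. The useful subgroup question is therefore for whom the HP adds more, which is a difference between arms within each subgroup. The planned sentence asks who changed most in one arm. That change is a sum: HP effect, pharmacist effect, change over time and regression to the mean. Two routes could produce a ranking unrelated to the HP.

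1. **Different pharmacist response by subgroup.** Pharmacists adjust drug regimens and use low-literacy medication lists (Pharmacists section). Medication regimen and health literacy are both listed subgroup factors, so response to the pharmacist could plausibly vary with them. This route needs no link between the factor and baseline A1c.
2. **Regression to the mean.** If a factor goes with temporarily high baseline A1c, that subgroup will fall further whatever care it receives.

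Under randomisation the Pharmacist arm is expected to carry both components equally, so contrasting with it removes them. The planned analysis leaves that arm out. At stake is how the exploratory findings can be interpreted, not the primary result.

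**Working it through.** **Inputs from the Sample size calculation.** SD 1.8, planned difference 1.0, cross-time correlation r = 0.30, ICC 0.02, cluster size 30, design effect 1.58, minimum 114 per group, 150 per group recruited, 10% dropout in each of two years.

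**Step 1. Reproduce the plan's figure.** The subgroup analysis has no stated figure, so the sample size serves as a check that the inputs are read correctly.
- SD of change = 1.8 × √(2 × (1 − 0.30)) = 2.13.
- n per group = 2 × (2.13 × (1.96 + 0.84))² / 1.0² = 71.2 before rounding of the inputs, so 72.
- Design effect = 1 + 29 × 0.02 = 1.58, and 72 × 1.58 = 113.8, so 114. The plan's figure reproduces, on change scores.

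**Step 2. Size of the regression route.** With equal SDs, the slope of change on baseline is r − 1 = −0.70. If two subgroups differ by g points at baseline and regress toward a common mean, their expected changes differ by 0.70 × g with no treatment effect at all.
- g = 0.5: 0.35 points.
- g = 1.0: 0.70 points.
- If the gap is stable, so that each subgroup regresses to its own mean: 0, whatever g is.

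The values of g are assumptions; the article gives none.

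**Step 3. Size of the pharmacist route.** An assumed 0.5-point difference in pharmacist response passes straight into the within-arm contrast as 0.50 points.

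**Step 4. Simulation.** Two equal subgroups, the same HP effect in both, 121 completers per arm (150 × 0.9 × 0.9 = 121.5), 4,000 replicates, two-sided 5% tests. Subgroups regress to a common mean and clustering is ignored.

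| Assumed baseline gap | Assumed gap in pharmacist response | Within-arm difference (size) | Within-arm false positives | Interaction mean | Interaction false positives |
|---|---|---|---|---|---|
| 0 | 0 | 0.01 | 5% | 0.00 | 5% |
| 0.5 | 0 | 0.35 | 14% | 0.01 | 5% |
| 1.0 | 0 | 0.71 | 45% | −0.01 | 5% |
| 0 | 0.5 | 0.50 | 26% | 0.01 | 6% |
| 0.5 | 0.5 | 0.83 | 58% | 0.02 | 5% |

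The arm-by-subgroup interaction stays centred on zero throughout; the within-arm contrast does not.

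**Step 5. Precision of the between-arm alternative.** For a 50/50 subgroup with n completers per arm, the effective number per arm and subgroup is n / 1.58 / 2, and the interaction SE is SD × √(4 / that number). The smallest detectable interaction is 2.80 × SE, and power for a 1.0-point interaction is Φ(1/SE − 1.96).
- Change scores, n = 121: 121 / 1.58 / 2 = 38.3; SE = 2.13 × √(4/38.3) = 0.69; detectable 1.9 points at 80% power; power about 31%.
- Change scores, n = 135 (150 × 0.9, one year of dropout, which fits a 12-month analysis): SE 0.65; detectable 1.8 points; power about 34%.
- Baseline-adjusted, residual SD = 1.8 × √(1 − 0.30²) = 1.72: SE 0.55 at n = 121 and 0.53 at n = 135; power about 44% and 48%.

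These carry the plan's design effect over to the interaction unchanged, which is itself an assumption.

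**The case against.** The strongest case on the other side has four parts.

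- **Regression to the mean is less certain than it looks.** A reader might multiply the slope of 0.70 by the 3.6 points between one SD above and one SD below mean baseline A1c, and infer a 2.5-point artefact. The article does not support that: baseline A1c is not a listed subgroup factor. Nor does every factor related to baseline A1c inherit the slope, since a subgroup with a stably higher level regresses to its own mean. Eligibility also rests on a reading from the past year, and no rule requires the baseline value itself to be 8% or higher, so some regression will have happened before baseline. No one is selected on blood pressure, LDL or behaviours. All of this stands, and the regression figures are therefore conditional.
- **The within-arm result is not devoid of HP information.** A reader might conclude that it reflects other effects instead of HP benefit. That is too strong: it contains the HP effect but cannot isolate it.
- **The analysis is exploratory, and the article does not say it will guide who gets an HP.** This is true, and it lowers the severity. But the label concerns strength of evidence and does not remove bias. The wording still fixes a quantity that does not answer the trial's question.
- **The interaction is poorly powered.** This also stands. Low power argues for modest claims, but not for a more precise estimate of something else.

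None of these answers the pharmacist route, which follows from the design and needs no selection on A1c.

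**Conclusion.** The point holds in a limited form. As worded, the analysis ranks change within one arm, and nothing else in the article supplies a between-arm contrast by subgroup. A subgroup could appear to benefit most when the HP effect is the same everywhere. How far this would distort the ranking is unknown, because the article gives no subgroup gaps. The illustrative distortions, 0.35 to 0.70 points by regression or 0.50 by pharmacist response, are roughly a third to two thirds of the planned 1.0-point effect. They rest on the assumed gaps and, for regression, on a common mean; with stable subgroup differences the regression part is zero. The primary arm comparison and the sample size are unaffected. Severity is minor.

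**What to change.** Replace the sentence with one along these lines: exploratory subgroup analyses by demographic factors, health literacy and medication regimen will estimate arm-by-subgroup interactions at 12 months in the planned mixed model, using both arms and adjusting for the baseline value of the outcome; the Pharmacist+HP minus Pharmacist difference will be reported with its confidence interval in each subgroup.

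Twelve months is the right time point because the Pharmacist arm gains HP support after that. Subgroup factors should be taken at their baseline values, since pharmacists change regimens during the trial.

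The cost is one sentence. The factors are already collected, and no visits or patients are added. The downside is wide intervals: about 31% power for a 1.0-point interaction on change scores with 121 completers per arm, and still under 50% with baseline adjustment and 135 completers. The exploratory label should stay, and a non-significant interaction should not be read as evidence that the HP effect is uniform.
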